**Nederlandse samenvatting protocol POCI-studie***Effect of multimodal Prehabilitation On Chronic limb-threatening Ischemia (POCI-study)*

De **POCI-studie** is een studie naar het effect van prehabilitatie bij de oudere patiënt ( $\geq 65$  jaar) met chronische ledemaat bedreigende ischemie (CLBI).

CLBI is de meest ernstige vorm van perifeer arterieel vaatlijden (PAV), die vooral op hogere leeftijd voorkomt en de kwaliteit van leven (KvL) ernstig vermindert. Ondanks steeds duurdere minimaal invasieve technieken (endovasculaire technieken) en operaties, en de daarmee gepaard gaande complicaties, is de kans op mortaliteit, afname van KvL en van het dagelijks functioneren hoog. Deze studie beoogt middels prehabilitatie, voorafgaand aan een interventie voor CLBI, een verbetering te geven in de (klinische) uitkomsten voor de patiënt, met name de duur van de ziekenhuisopname en de KvL. Verder worden een afname in zorgkosten en toename van verplaatste zorg naar huis beoogd. In dit project is er specifiek aandacht voor KvL van patiënt en mantelzorger, shared decision making (SDM) en de mantelzorgerbelasting. De ervaringen van de patiënt en de mantelzorger worden gebruikt bij de implementatie van de prehabilitatie. De studie opzet is multicenter en gerandomiseerd, met een kosteneffectiviteitsanalyse.

Patiënten boven de 65 jaar met CLBI die hiervoor een behandeling zullen ondergaan, worden bij presentatie in het ziekenhuis gerandomiseerd. Afhankelijk hiervan zullen zij wel of geen prehabilitatie krijgen, voorafgaand aan hun ingreep. Het prehabilitatie programma is een multidisciplinair programma en een samenwerking tussen de vaatchirurgie, geriatrie, fysiotherapie en diëtik. Het prehabilitatie programma zal direct starten na randomisatie en duurt tenminste 2 weken, alvorens de interventie zal plaatsvinden. Eerder observationeel onderzoek in het Amphia ziekenhuis heeft aangetoond dat deze duur van prehabilitatie bij patiënten met kritieke ischemie veilig kan worden toegepast. Middels uitgebreide screening en daarop aansluitend het aanbieden van (spier- en kracht) oefeningen, dieetadviezen, delierpreventieve maatregelen, suppletie van vitaminen en het behandelen van een preoperatieve anemie (indien van toepassing), wordt de patiënt geoptimaliseerd om in betere conditie de behandeling te ondergaan.

De studieopzet betreft evaluatie van een relatief nieuwe vorm van standaard zorg welke in het Amphia ziekenhuis reeds geïmplementeerd is, maar ook zal worden geïmplementeerd in het Elisabeth Tweesteden ziekenhuis en het Meander medisch centrum. De primaire uitkomstmaat is de lengte van de ziekenhuisopname. Secundaire uitkomstmaten zijn het aantal postoperatieve complicaties, de kwaliteit van leven van zowel patiënten als hun mantelzorgers en de lasten die mantelzorgers ervaren van de prehabilitatie. Tevens zal er een kosteneffectiviteitsanalyse worden verricht. Ten slotte zal er ook specifieke aandacht zijn voor de ervaringen en voorkeuren van patiënten en mantelzorgers ten aanzien van SDM.

**LIST OF ABBREVIATIONS AND RELEVANT DEFINITIONS**

|                 |                                                                                                                    |
|-----------------|--------------------------------------------------------------------------------------------------------------------|
| AE       | Adverse Event                                                                                               |
| AFS      | Amputation Free Survival                                                                                    |
| AR       | Adverse reaction                                                                                            |
| ASA      | American Society of Anesthesiologists                                                                       |
| BMI      | Body Mass Index                                                                                             |
| CCI      | Charlson Comorbidity Index score                                                                            |
| CCMO     | Central Committee on Research Involving Human Subjects; in Dutch: Centrale Commissie Mensgebonden Onderzoek |
| CFS      | Clinical Frailty Score                                                                                      |
| CGA      | Comprehensive Geriatric Assessment                                                                          |
| CLTI     | Chronic Limb Threatening Ischemia                                                                           |
| CSI      | Caregiver Strain Index                                                                                      |
| DEMMI    | The ‘De Morton Mobility Index’                                                                              |
| DM       | Decision Making                                                                                             |
| DOSS     | Delirium Observation Screening Score                                                                        |
| DSMB     | Data Safety Monitoring Board                                                                                |
| EPD      | Electronic Patient Dossier                                                                                  |
| EQ-5D-5L | EuroQol 5 dimensions 5 level                                                                                |
| GCP      | Good Clinical Practice                                                                                      |
| GDPR     | General Data Protection Regulation; in Dutch: Algemene Verordening Gegevensbescherming (AVG)                |
| G8-score | Geriatric-8 score                                                                                           |
| IB       | Investigator’s Brochure                                                                                     |
| IC       | Informal Caregiver                                                                                          |
| IMDD     | Investigational Medical Device Dossier                                                                      |
| iMCQ     | iMTA Medical Consumption Questionnaire                                                                      |
| LOS      | Length of Hospital Stay                                                                                     |
| METC     | Medical research ethics committee (MREC); in Dutch: medisch-ethische toetsingscommissie (METC)              |
| MIP      | Maximal inspiratory and pressure                                                                            |
| MMSE     | The Mini-Mental State Examination                                                                           |
| MNA-SF   | Mini Nutritional Assessment – Short Form                                                                    |
| MVE      | Multidisciplinary Vascular surgical outpatient clinic for the Elderly                                       |
| OS       | Overall Survival                                                                                            |

|                         |                                                                                                                                                                                                                                                                                                                                                  |
|-------------------------|--------------------------------------------------------------------------------------------------------------------------------------------------------------------------------------------------------------------------------------------------------------------------------------------------------------------------------------------------|
| PAD              | Peripheral Arterial Disease                                                                                                                                                                                                                                                                                                               |
| PICS             | Perceived Involvement in Care Scale                                                                                                                                                                                                                                                                                                       |
| PIF              | Patient Information Folder                                                                                                                                                                                                                                                                                                                |
| PTA              | Percutaneous transluminal angioplasty                                                                                                                                                                                                                                                                                                     |
| PTFE             | Polytetrafluoroethylene                                                                                                                                                                                                                                                                                                                   |
| PVR              | Pulse Volume Recording                                                                                                                                                                                                                                                                                                                    |
| QoL              | Quality of Life                                                                                                                                                                                                                                                                                                                           |
| RCT              | Randomized Controlled Trial                                                                                                                                                                                                                                                                                                               |
| Review committee | Medical research ethics committee (MREC) or CCMO                                                                                                                                                                                                                                                                                          |
| (S)AE            | (Serious) Adverse Event                                                                                                                                                                                                                                                                                                                   |
| SDM              | Shared Decision Making                                                                                                                                                                                                                                                                                                                    |
| SNAQ-RC          | Short Nutritional Assessment Questionnaire for the Residential Care                                                                                                                                                                                                                                                                       |
| Sponsor          | The sponsor is the party that commissions the organisation or performance of the research, for example a pharmaceutical company, academic hospital, scientific organisation or investigator. A party that provides funding for a study but does not commission it is not regarded as the sponsor, but referred to as a subsidising party. |
| SUSAR            | Suspected Unexpected Serious Adverse Reaction                                                                                                                                                                                                                                                                                             |
| TASC-II          | Trans-Atlantic Inter-Society Consensus Document on Management of Peripheral Arterial Disease II                                                                                                                                                                                                                                           |
| TU               | Tilburg University                                                                                                                                                                                                                                                                                                                        |
| TUG              | Timed Up and Go                                                                                                                                                                                                                                                                                                                           |
| UAVG             | Dutch Act on Implementation of the General Data Protection Regulation; in Dutch: Uitvoeringswet AVG                                                                                                                                                                                                                                       |
| VNP              | Vascular Nurse Practitioner                                                                                                                                                                                                                                                                                                               |
| V-POSSUM         | Vascular-Physiological and Operative Severity Score for the enUmeration of Mortality and Morbidity                                                                                                                                                                                                                                        |
| WHOQoL-BREF      | World Health Organization Quality of Life Brief Version                                                                                                                                                                                                                                                                                   |
| WMO              | Medical Research Involving Human Subjects Act; in Dutch: Wet Medisch-wetenschappelijk Onderzoek met Mensen                                                                                                                                                                                                                                |

## SUMMARY

**Rationale:** Chronic limb-threatening ischemia (CLTI) is the most severe form of peripheral arterial disease (PAD). CLTI primarily occurs in older adults and is associated with the need for (multiple) hospital admissions and significantly reduces the quality of life (QoL). Despite the increase of (more expensive) minimally invasive techniques (endovascular procedures) and surgeries, the associated complications, the risk of mortality, reduction in QoL, and decline in daily functioning remain high.

**Objective:** The aim of this study is to minimize the length of hospital stay (LOS) and improve patients' (clinical) outcomes, particularly their QoL, through prehabilitation prior to a CLTI intervention. Additionally, we aim to reduce healthcare costs and to improve the process of shared decision making (SDM).

**Study design:** This is a randomized multicentre study, with a cost-effectiveness analysis.

**Study population:** All CLTI patients aged 65 years or older presenting to the vascular surgeon with a new onset of CLTI who are planned for surgical or endovascular revascularization are screened for eligibility. Their primary IC will also be asked to participate in the study.

**Intervention (if applicable):** All patients undergo a general health screening by a vascular nurse practitioner (VNP) or researcher at the Multidisciplinary Vascular surgical outpatient clinic for the Elderly (MVE). Afterwards patients randomized to the intervention group are offered a prehabilitation program, starting directly at the MVE. Patients are referred to a physiotherapist and if indicated also to a geriatrician, dietician and a quit smoking coach. All will collaborate to optimize the patient's preoperative condition, to shorten the LOS and improve QoL of both patient and IC. In summary the prehabilitation program consists of: physical training, lifestyle advice, diet advice and supplements, iron infusion (Ferinject) in case of an iron deficiency anaemia and a comprehensive geriatric assessment (CGA).

**Main study parameters/endpoints:** The primary outcome is the LOS. Secondary outcomes will be QoL of the patient and their IC, 6-month mortality, postoperative complications, hospital readmission, 2level of perceived SDM and preferred participation in SDM of the patient and their IC, perceived and preferred roles in decision making (DM) of the patient and their IC and cost-effectiveness.

**Nature and extent of the burden and risks associated with participation, benefit and group relatedness:** The burden for all participants consists of the visit to the MVE, drawing a blood sample and filling in questionnaires at baseline, at the second visit to the vascular surgeon and 6 months after revascularization. Patients in the intervention group are provided with home-based exercises by a physiotherapist. These exercises take time and should be performed daily and written down in a diary. If indicated they also receive dietary advice and advices from the geriatrician to take into account at home.

## 1. INTRODUCTION AND RATIONALE

In the face of an aging population, the prevalence of CLTI among elderly persons of 65 years and older has become a major public health concern. CLTI, a severe form of PAD, is characterized by atherosclerotic occlusion of the arteries supplying the lower extremities, leading to ischemic rest pain and/or tissue damage (1). Annually, 500-1000 new cases of CLTI occur per 1 million people in Europe.

Revascularization is the primary treatment for CLTI and current guidelines advise to do this as soon as possible to prevent major limb amputation. However, the treatment of CLTI is associated with reduced QoL of both patient and their ICs, long duration of hospital stays, intensive wound care, high chance of discharge to a nursing home and places a high burden on the IC (2). Thereby, up to a quarter of the CLTI patients is at risk for major amputation despite revascularization attempts.

Recognizing the need for a strategy to minimize the risk of developing complications, diminish the LOS and increase QoL, multimodal prehabilitation has emerged as a promising preoperative approach within vascular surgery. Prehabilitation is the all-encompassing term of preoperative optimization of the patient's functional capacity and resilience, in order to reduce postoperative complications (3). Interventions include physical, mental, functional and nutritional optimization.

The decision on the treatment of CLTI should be made in a SDM process. SDM increases patients' knowledge of treatment options, initiates accurate risk perception, improves patient satisfaction and reduces undesired care in certain categories of patients (4). However, it is known that SDM is still not common practice in vascular surgery and thorough research in this field is lacking.

Our research group has extensive experience with prehabilitation, and demonstrated that prehabilitation in older CLTI patients is safe (5-7). This previous research informed a paradigm shift in vascular surgery, from revascularization as soon as possible, to time for prehabilitation. However, the research was monocenter and observational. A multicenter randomized controlled trial (RCT) and cost-effectiveness study is lacking. Therefore, this POCI-study is designed, a multicenter RCT studying the effect of prehabilitation on LOS, postoperative complications, hospital readmission and QoL, including a cost effectiveness analysis. In addition, we aim to investigate the experiences and preferences of both patients and ICs with (S)DM concerning CLTI treatment in the outpatient vascular surgical clinic.

## 2. OBJECTIVES

### Primary Objective:

The aim of this study is to minimize the LOS in elderly patients of 65 years and older with CLTI that require surgical or endovascular revascularization. Our hypothesis is that by implementing a prehabilitation program focused on preoperative optimization of the patient's functional capacity, the LOS will decrease with 25% compared to patients not attending the program.

### Secondary Objective(s):

Secondary, we aim to reduce the number of postoperative complications, the amount of hospital readmissions, 6-month mortality and the burden on the IC (using the Caregiver Strain Index (CSI)). In addition, our goal is to improve the QoL of both patient and their IC (QoL, measured by using the WHOQoL-BREF and the health related QoL measured by using the EQ-5D-5L). The level of perceived SDM of the patient and their IC (using the CollaboRATE), perceived and preferred roles in decision making (DM) of the patient and their IC (using the Adapted Control Preference Scale (ACPS)) and preferred participation in SDM of the patient and their IC (using the Perceived Involvement in Care Scale (PICS)) will be measured. Lastly, we aim to reduce health-care costs by implementing the prehabilitation program.

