### 3. STUDY DESIGN

An RCT with a cost-effectiveness analysis, will be performed in three non-university large teaching hospitals in the Netherlands (Amphia Hospital Breda, Elisabeth Tweesteden Hospital Tilburg and Meander Medical Center Amersfoort), during the period of November 2025 to May 2028. All patients of 65 years or older, with a new onset of CLTI presented at the outpatient clinic of the vascular surgeon, who are planned for surgical or endovascular revascularization and who meet the in- and exclusion criteria are asked to participate in the study. In addition, their primary IC will also be requested to take part in the study. A primary IC is defined as follows: the person most involved in caring for the CLTI patient and supporting at least one instrumental activity of daily living of the patient or defined as the contact who supports in decisions by the patient. Patients can still be included, if their primary IC refuses participation. However, primary ICs can only be included together with a patient.

At the outpatient clinic information about the POCI-study is provided by a VNP or researcher and patients and ICs receive an information folder. They are called by telephone the next day by a researcher or VNP to ask if they want to participate. If so, oral informed consent will be obtained by the researcher or VNP and patients are randomized immediately upon inclusion, either into the prehabilitation group or the control group, the latter receiving the standard of care. Their IC will automatically be randomized to the same group. Within a few days all patients undergo a general health screening by a VNP or researcher and a blood sample will be taken as part of the standard care. Written informed consent will be obtained during this visit. Afterwards patients receive three questionnaires: the WHOQoL-BREF, the EQ-5D-5L and the iMTA Medical Consumption Questionnaire (iMCQ) (t=0). ICs are also asked to fill in two questionnaires: the WHOQoL-BREF, and the CSI (t=0). Afterwards, patients randomized into the intervention group are referred to the prehabilitation program where they are assessed by a physiotherapist and if indicated also a geriatrician, dietician or a quit smoking coach. The prehabilitation program will take two weeks, considering both the time needed to possibly reach significant results with the program and the time in which treatment is planned and must take place.

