After treatment planning is complete, the vascular surgeon will discuss this plan with patients and their IC in a second visit to the outpatient clinic. Afterwards both patient and IC are asked to fill in three questionnaires, regarding the SDM process: the CollaboRATE, the ACPS and the PICS (tSDM=0).

Patients and their ICs will be included during a period of 2 years and will stay in follow-up for 6 months. At the 6-months follow-up patients are asked to fill in four questionnaires: the

WHOQoL-BREF, the EQ-5D-5L, the iMCQ and a process evaluation form designed by the researchers (t=1). ICs are asked to fill in three questionnaires: the WHOQoL-BREF, the CSI and a process evaluation form (t=1).

Inclusion of the patient and their IC will be on the day after the first outpatient clinic visit. This way the prehabilitation starts within a few days, parallel to the treatment planning (imaging, multidisciplinary meeting, planning for surgery or endovascular treatment) and there will be no delay in the treatment schedule.

FIGURE 1 – FLOWCHART POCI-STUDY

[figure not shown]

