#### 8.1.2 Secondary study parameters/endpoints

Secondary outcomes (Appendix 1-Uitkomstmaten) will be postoperative complications, hospital readmission rate, 6-month mortality, QoL of both patient and their informal caregiver (measured by using the WHOQoL-BREF), the health related QoL of patients (measured by using the EQ-5D-5L), burden on informal caregiver (using the CSI), the level of perceived SDM of the patient and their IC (using the CollaboRATE), perceived and preferred roles in DM of the patient and their IC (using the ACPS), preferred participation in SDM of the patient and their IC (using the PICS), a cost-effectiveness analysis will be performed (using the iMCQ) and a process evaluation will take place (using an effect evaluation form designed by the research group). For the forms used to measure these endpoints, see 'F1-Vragenlijsten.

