#### Second visit to the outpatient clinic (treatment)

After treatment planning is complete, the vascular surgeon will discuss this plan with patients and their IC in a second visit to the outpatient clinic. Afterwards both patient and IC are asked to fill in three questionnaires, regarding the SDM process: the CollaboRATE, the ACPS and the PICS (tSDM=0).

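### The secondary endpoint on preferred participation in shared decision making is measured only with a scale that the protocol itself names as one of perceived involvement

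*Protocol*

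**What the plan says.** The protocol names three instruments for decision making, each for both the patient and the informal caregiver (IC). Section 2, Secondary Objective(s), assigns them as follows:

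- CollaboRATE: "The level of perceived SDM of the patient and their IC (using the CollaboRATE").
- ACPS: "perceived and preferred roles in decision making (DM) of the patient and their IC (using the Adapted Control Preference Scale (ACPS")).
- PICS: "preferred participation in SDM of the patient and their IC (using the Perceived Involvement in Care Scale (PICS")).

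Section 8.1.2 repeats the last pairing as "preferred participation in SDM of the patient and their IC (using the PICS"), and section 10.2 carries it into the statistical analysis. The list of abbreviations expands PICS in the same way as section 2. The Summary lists preferred participation as a secondary outcome without naming an instrument.

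On timing, section 3 says of the second visit, where the surgeon discusses the treatment plan: "Afterwards both patient and IC are asked to fill in three questionnaires, regarding the SDM process: the CollaboRATE, the ACPS and the PICS (tSDM=0"). Section 8.3 says the same. The t=0 forms contain no decision-making instrument. For patients: "Afterwards patients receive three questionnaires: the WHOQoL-BREF, the EQ-5D-5L and the iMTA Medical Consumption Questionnaire (iMCQ) (t=0"). For ICs: "ICs are also asked to fill in two questionnaires: the WHOQoL-BREF, and the CSI (t=0"). The 6-month forms contain none either.

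**The concern.** The endpoint is labelled as a preference, and its only instrument is named as a measure of perception. How involved people felt and how involved they wanted to be are separate quantities, and one cannot stand in for the other.

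The protocol depends on this distinction. Section 1 and the part of section 8.3 on the information brochure state an aim covering both experiences and preferences. If the PICS score is analysed under its present label, a difference between arms in how involved people felt would be published as a difference in what they wanted. Readers of the results would have no reason to suspect it.

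A statistical analysis plan would not normally settle this. Which instrument measures which endpoint is fixed in the objectives and endpoint sections of the protocol, and an analysis plan would inherit the pairing.

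**Working it through.** No arithmetic applies: the point depends on no sample size, effect size or error rate. The check is to set construct, instrument and timing side by side.

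| Construct as labelled | Instrument | What the protocol's own wording says it covers | When given |
|---|---|---|---|
| Perceived shared decision making | CollaboRATE | Perception | Once, after the second visit |
| Perceived and preferred roles | ACPS | Perception and preference | Once, after the second visit |
| Preferred participation | PICS | Perceived involvement (by its name) | Once, after the second visit |

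1. **Do label and instrument agree?** In the first two rows they do. In the third they do not.
2. **Is it a single slip?** No. The pairing stands in sections 2, 8.1.2 and 10.2. The Summary repeats the label alone.
3. **Does the protocol use perceived and preferred interchangeably?** No. Section 2 names both, as distinct things, for the ACPS within the same sentence.
4. **Is another instrument assigned to preferred participation?** No. The PICS is the only one.
5. **Would the score be analysed under this label?** Yes. Section 10.2 lists it among the secondary parameters to be analysed by regression, in a trial that compares two arms.
6. **Does any other instrument carry preference?** Yes. The ACPS is said to cover preferred roles, so the preference aim is not left without a measure.
7. **When is the ACPS given?** Only at "regarding the SDM process: the CollaboRATE, the ACPS and the PICS (tSDM=0"), after the surgeon has presented the plan. By then patients in the prehabilitation arm may have had contacts with a physiotherapist, geriatrician or dietician that controls did not have (sections 3, 5 and 8.3), and the trial is unblinded (section 8.2). A stated preference may therefore be coloured by the consultation and by the arm.
8. **Would t=0 be cleaner?** Partly. Section 3 places the t=0 forms before referral to the programme and before the second visit, but after the first surgeon visit, after randomisation and after the general health screening.

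**The case against.** The strongest objection is that the PICS items are not in evidence. The forms are in a separate questionnaire file that is not part of the document, so nobody can show from the protocol what the items ask. The error could also lie on either side: the label may be wrong, or the instrument may be. Both points stand. They limit the claim to a contradiction between the endpoint's label and the scale's stated name. They do not remove it, because the protocol would need correcting even if the items turned out to ask about preference. They also mean that the correction must allow for both possibilities.

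A reader might go further and infer that all of the preference results would really be experience, because the ACPS is given after the talk. The document does not support that. It describes the ACPS as covering preferred roles, and late timing does not turn it into a measure of experience.

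A reader might also infer that agreement between preferred and perceived role would be inflated. No section plans an agreement analysis, and nothing in the document shows the direction or size of any drift: a dissatisfied respondent could move away from the role just experienced. Drift that was similar in both arms need not bias the comparison between them. Sections 3 and 8.3 agree on the timing, and the protocol nowhere claims to capture preference before the consultation. The timing is a design choice with a possible weakness, not an error.

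**Conclusion.** The endpoint definition is wrong as written. Sections 2, 8.1.2 and 10.2 give a preference endpoint to a scale that the protocol calls a scale of perceived involvement, and give it no other instrument. Following the plan would present perceived involvement as preference.

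The scope is one secondary endpoint, collected in up to 300 patients and their participating ICs. The primary endpoint, its analysis and the sample size are untouched. The conclusion rests on one assumption: that the scale measures what its stated name says.

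The timing of the ACPS is a lesser matter. The preferred role may be influenced by the consultation and the allocation, but the document does not establish that it would be, and no figure can be put on it from what is given.

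**What to change.** **Needed.** Reconcile label and instrument in the Summary and in sections 2, 8.1.2 and 10.2, in one of two ways:

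- Rename the PICS endpoint as perceived involvement in care, and take preference from the preferred-role part of the ACPS. This is a wording amendment: the same data are collected and no participant is affected.
- If preferred participation is wanted as an endpoint of its own, assign it an instrument that measures preference. This adds a form, and it should be settled early in the two-year recruitment period, because those who have already passed the time point cannot supply the answer afterwards.

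The PICS items in the questionnaire file should be checked before choosing.

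**Optional.** Ask the ACPS preferred-role item with the t=0 forms, keeping the perceived-role item, CollaboRATE and PICS after the second visit. This places the stated preference before the treatment talk and before the programme, though still after randomisation. The cost is a slightly longer t=0 form for patients and ICs.
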